## Methods

### Study design

This is a prospective, multicenter, analyst-blinded, randomized controlled trial. Subjects will be grouped into one healthy control group and two parallel experiment arms, as follows: (1) people without PCOS (healthy control group), (2) patients diagnosed with PCOS based on clinical indices (experimental group 1), and (3) patients diagnosed with PCOS based on metabolomic indices (experimental group 2). A total of 276 participants, including 60 people without PCOS and 216 patients with PCOS, will be recruited. The 216 patients with PCOS will be randomly assigned to the two experimental (diagnosis) groups in a 1:1 ratio. After group assignment, medical detection results, relative information, and biological samples will be collected from all three groups. Additionally, the blood samples from all participants will be tested using metabolomic methods for further study, while the analysis results will be totally blinded to all participants and their research physicians. Based on our previous study [3], we will categorize patients with PCOS into two subgroups: patients with hormone metabolism disorders (subgroup 1) and patients with lipid metabolism disorders (subgroup 2).

The two diagnosis groups will be automatically divided into the two different subgroups according to patient characteristics. The main difference is that in group 1, diagnosis will be based on clinical indices [1], such as clinical signs and symptoms and ultrasonography findings, while in group 2, diagnosis will be based on metabolomic indicators. All patients will receive treatment according to their subtype group, and the treatment will consist of Diane-35 or metformin. The intervention period for all experimental groups will be 6 months, and the results will be evaluated after the completion of three constant treatment sessions (3 months).

Outcomes will be assessed, and the data will be analyzed by someone blinded to the assignment of participants. The study design is shown in Fig. 1, and the timeline is presented in Figs. 2 and 3.

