#### Metabolomic index group

Most of the interventions for the metabolomic index group will be similar to those for the clinical index group. The main difference is that the division of the subgroups will be based on metabolomic indices. The physicians in this group will be informed of the allocation of participants to the subgroups and will provide the corresponding treatment scheme to all participants. The physicians will not be allowed to change the scheme during the trial and will remain blinded to the metabolomic results to minimize the possibility of any influence on treatment decisions.

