### Outcome measurements

The healthy control group will remain enrolled in the trial until all their samples are collected. For the experimental groups, the primary outcome will be the changes in their relative PCOS condition evaluated using clinical indices. The main clinical index that will be evaluated is the LH/FSH ratio.

Secondary outcomes will be assessed using other indices, signs, and symptoms, as described in the 2018 Chinese Endocrine Society clinical practice consensus on PCOS [1] such as sex hormone-related indices (FSH, LH, prolactin, estradiol, progesterone, testosterone, anti-Müllerian hormone (AMH), and vitamin D), blood lipid-related indicators (total cholesterol, triglycerides, HDL, LDL, Apo A1, Apo B, lipoprotein(a), free fatty acids, and high-sensitivity C-reactive protein), and endocrine-related indicators (glucose and insulin (at 0, 30, and 120 min) and blood uric acid). To help evaluate the outcomes, three metabolic markers will also be used, namely, palmitoyl sphingomyelin, cyclic guanosine monophosphate, and DHEAS. Ultrasound results will also be evaluated, and the number and diameter of follicles in both ovaries will be measured.

Safety outcomes will include any severe impairment in liver function or inability of the patient to tolerate symptoms (e.g., nausea and vomiting caused by metformin) related to the therapeutic drugs. Such outcomes will be monitored after each treatment session (1 month) using the hepatic function test. An exploratory outcome will be complete recovery from PCOS after treatment within 26 weeks.

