### Statistical analyses

The dataset will include a safety set, a full analysis set (FAS), and a per-protocol set. The safety set is designed for participants who will be randomly assigned to receive at least one session of treatment. The FAS will include all medical data related to the trial and will indicate the intervention conducted; however, participants who miss the primary outcome evaluation will be excluded. In the per-protocol set, participants will be included if they receive at least three constant sessions of treatment.

In this trial, the FAS will be used for the basic analysis. For missing data, we will employ the imputation adjustment approach, and the last observation analysis will be selectively used to handle the missing data.

A sensitivity analysis will then be used to compare the results of the per-protocol analysis and the different intervention analyses to evaluate the impact of the missing data on the trial results.

Descriptive statistics about quantitative indicators, such as means, standard deviations, medians, minimums, and maximums, will be presented. Variance analysis will be used to compare the quantitative indices among the different groups (healthy control group and experimental groups 1 and 2), and the Student-Newman-Keuls test will be used to analyze the two subgroups.

Classification indicators will be described by the number and percentage of each category. The chi-squared test or exact probability method will be used to compare the qualitative indices among the three groups, and the chi-squared segmentation method will be used to compare the two pairwise subgroups.

SPSS version 21.0 will be used to analyze all trial data. All statistical tests will be double-sided, and statistical significance will be considered when the *p* value is ≤ 0.05.

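### The stated three-group ANOVA includes healthy controls, and no direct test of group 1 against group 2 on change in LH/FSH is fixed

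*Protocol article*

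**What the plan says.** All references are to the Protocol article.

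- **Statistical analyses, quantitative data:** "Variance analysis will be used to compare the quantitative indices among the different groups (healthy control group and experimental groups 1 and 2"). The same sentence continues that "the Student-Newman-Keuls test will be used to analyze the two subgroups".
- **Statistical analyses, categorical data:** a test across the three groups comes first, after which "the chi-squared segmentation method will be used to compare the two pairwise subgroups".
- **Outcome measurements:** "For the experimental groups, the primary outcome will be the changes in their relative PCOS condition evaluated using clinical indices". The next sentence adds: "The main clinical index that will be evaluated is the LH/FSH ratio". On the healthy women, the section says: "The healthy control group will remain enrolled in the trial until all their samples are collected".
- **Study design:** randomisation is 1:1 between experimental groups 1 and 2. The 60 healthy women are not randomised. The word subgroup is introduced here for "patients with hormone metabolism disorders (subgroup 1) and patients with lipid metabolism disorders (subgroup 2").
- **Metabolomic index group:** in this arm "the division of the subgroups will be based on metabolomic indices", whereas the clinical index group is divided on clinical indices.

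**The concern.** The trial asks whether managing patients by one classification gives a better result than managing them by the other. That is a contrast between two randomised arms. The overall test named in the plan has a different null hypothesis: that healthy women, arm 1 and arm 2 all share one mean. It can be rejected because women with PCOS differ from healthy women, which is not in question.

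The follow-up step could supply the missing contrast, but its target is unclear. If it means the hormone and lipid phenotypes, the plan contains no test of the randomised comparison. At stake are a significant result that says little about the two diagnostic strategies, and a choice of test for the primary outcome that stays open until the data are seen.

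**Working it through.** **Inputs from the article.** 60 controls and 108 per arm, dropout 20%, two-sided 0.05 and power 0.80 (Sample size calculation; Statistical analyses).

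**Assumptions, not in the article.** No LH/FSH difference or SD is given. I take SD 1 in every group, all 60 controls evaluable, and 108 × 0.8 = 86.4, so 86 evaluable per arm. The arm difference for which 86 per arm gives 80% power is (1.96 + 0.842) × √(2/86) = 0.427 SD. It serves as a reference effect only.

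**1. Overall F test with identical arms, controls δ SD away.** The noncentrality is λ = [60 × 172 / 232] × δ² = 44.48 δ², with 2 and 229 degrees of freedom and critical value 3.035.

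| δ | λ | P(significant) |
|---|---|---|
| 0 | 0 | 0.05 |
| 0.25 | 2.78 | 0.297 |
| 0.5 | 11.12 | 0.852 |
| 0.8 | 28.47 | 0.999 |

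A simulation of 20,000 runs gave 0.052, 0.293, 0.854 and 0.999.

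**2. Student-Newman-Keuls step, phenotype reading.** Study design uses subgroup for the hormone and lipid phenotypes. On that usage the step compares phenotypes, and no stated test sets group 1 against group 2.

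**3. Student-Newman-Keuls step, pairwise reading.** With harmonic-mean group size 3/(1/60 + 2/86) = 75.1 and studentised-range points 2.787 (two means) and 3.336 (three means), the observed arm difference needed is:

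- 2.787/√75.1 = 0.32 SD when the control mean lies outside the two arm means, provided the full range of the three means first exceeds 0.38 SD;
- 3.336/√75.1 = 0.38 SD when the control mean lies between them;
- 1.974 × √(2/86) = 0.30 SD for a direct two-arm t test.

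Simulated with controls 0 to 1 SD from arm 1:

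| | Student-Newman-Keuls, arm 1 v arm 2 | Direct t test |
|---|---|---|
| Type I error | 0.018 to 0.038 | about 0.05 |
| Power at 0.427 SD | 0.635 to 0.760 | about 0.80 |

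**4. Use of baseline in a two-arm test.** At 0.427 SD, power is Φ(0.427/(s√(2/86)) − 1.96), where r is the baseline-outcome correlation, s = √(2(1−r)) for a change score and s = √(1−r²) for ANCOVA.

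| r | Change score | ANCOVA |
|---|---|---|
| 0.3 | 0.66 | 0.84 |
| 0.5 | 0.80 | 0.90 |
| 0.7 | 0.95 | 0.98 |

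An unadjusted final value gives 0.80 throughout.

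**The case against.** The strongest defence is that Student-Newman-Keuls is a pairwise procedure that normally follows a multi-group ANOVA, and the categorical paragraph has the same shape: a three-group test, then a pairwise one. On that reading group 1 against group 2 is tested. This stands as one possible reading, and it rules out some stronger criticisms that a reader might infer:

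- *That the three-group ANOVA is the only stated test.* It is not; the same sentence adds the follow-up step.
- *That the 85% and 99.9% figures are false-positive rates for the trial's question.* They belong to the overall F test. On the pairwise reading the arm comparison errs below 0.05, and the cost is power.
- *That baseline is ignored.* The outcome is a change, which uses baseline. What is not stated is baseline as a covariate, and an article may leave that to an analysis plan. I raise it only as part of the replacement analysis.
- *That the plan's subgroup tests are biased by regression to the mean.* The article states no comparison of arms within a subtype. LH/FSH as a classifying index comes from the Background's account of practice in China. Any figure would need reliabilities and correlations that the article does not give.

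It can also be said that controls, with no follow-up visits described in the text, have no change value and so cannot enter an ANOVA of change. The schedule figure is not shown, so this cannot be settled. If it is right, the primary outcome has no assigned test at all, and the same fix is needed.

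**Conclusion.** The point holds. The article states an analysis of quantitative outcomes that does not match its own primary outcome, and it does not fix the randomised two-arm comparison. This is more than detail left to an unseen analysis plan, because the tests that are named include a non-randomised, untreated group and a follow-up step with two incompatible readings.

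The size depends on the reading. On the phenotype reading, the randomised contrast is untested, and the overall F test cannot stand in for it. On the pairwise reading, the loss is moderate: about 4 to 16 percentage points of power (0.80 less 0.76 or 0.64), with a result that shifts according to where the healthy women lie. These figures rest on the assumed SD of 1, 60/86/86 evaluable, harmonic-mean group size and the 0.427 SD reference effect. The mismatch itself does not depend on them.

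**What to change.** State one primary analysis: experimental group 1 against group 2 on LH/FSH, by ANCOVA of the post-treatment value on randomised arm with week 0 LH/FSH as covariate, reported with a 95% CI. Centre may be added, and a log scale is optional. Use the evaluation time point that the protocol designates, and name it in the same sentence, since the article mentions both an evaluation after three months and a 6-month treatment period.

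Move the healthy controls, in the chi-squared tests as well as the ANOVA, to a separate descriptive comparison at baseline. Replace the Student-Newman-Keuls wording, or say exactly which groups it compares.

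If arms are to be compared within subtype, define subtype in both arms by the same baseline classifier. The week 0 metabolomic class is available for this, because Study design has all participants' blood tested by metabolomic methods.

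The cost is analysis-plan wording only. A change in LH/FSH already requires the week 0 value, so no new data are needed. The wording should be settled before unblinding.

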**Fig. 3 Fig3:**
[figure not shown]
The schedule of forms and procedures, according to the Protocol Items. Physical examination includes: ultrasonography of bilateral ovarian anad clinical biochemical indicators. Clinical biochemical indicators routine urine tests, routine blood tests, liver function, pregnancy tests, LH/FSH ratio, sex hormone related indicators blood lipid related indicators and endocrine related indicators. There are twenty-five clinical biochemical indexes including eight sex hormone-related indexes: FSH, LH, PRL, E2, P, Ts, AMH, AND vitD; nine blood lipid indicators: TC, TG, HDL, LDL, ApoA1, Apo B, Lp(a), FFA, hsCRP; seven endocrine-related indicators: GLU (0h, 30min, 120min), INS (0h, 30min, 120min), BUA. The main elevation index was LH/FSh ratio. Note: ultrasonography examination is scheduled for the 14th day of menstruation, if the patient with rare ovulation has follicular diameter > 10mn or luteal appearance, should be reviewed in the subsequent menstrual cycle. Unmarried women without sexual life suggested abdominal B ultra. All blood samples will be collected on an empty stomach within 72 hours from the first day of menstruation

The main treatment center will be the Department of Endocrinology and Metabolism of the Affiliated Wuxi People’s Hospital of Nanjing Medical University, which will enroll 60 participants for the healthy control group and 108 participants who, in the experimental group (108/216), will be randomly assigned between the two experimental groups. Two other treatments centers—Wuxi Maternal and Child Health Centers Clinical Hospital and Jiangyin People’s Hospital—will enroll the other 108 participants, who will also be randomly assigned between the two experimental groups.

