### Sample size calculation

Based on the literature and findings from a small pilot study that used metabolomic techniques, the sensitivity and specificity required to classify the control and PCOS groups will be 100% and 86%, respectively. The corresponding values between the control group and subgroup 1 will be 96.7% and 100%, respectively, while those between the control group and subgroup 2 will be 100% and 86.2%, respectively. The sensitivity and specificity for dividing PCOS into two different subtypes will be 90.9% and 87.5%, respectively. To meet the lower statistical limit, each subgroup will include at least 30 participants.

According to a presumptive maximum dropout tolerance of 20%, with a significance level of 0.05 and a power of 0.80, we calculate the required sample size for the experimental groups to be 216. In this trial, 60 people will be assigned to the healthy control group and 108 people to each experimental group across the three centers.

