### Study limitations

The main difficulty inherent to this trial is making a consistent diagnosis in experimental group 1 because the diagnosis will be made by several different physicians. To address this problem as much as possible, our group will organize a diagnosis team consisting of three professional physicians who have majored in endocrinology and metabolism or gynecological endocrinology for at least 10 years and achieved the position of assistant director . If the clinical research physicians cannot diagnose the participant’s subtype, the case will be submitted to the team for a final diagnosis. Another methodological difficulty is ensuring that the treatment complies with the scheme. In this trial, we will ensure that medication reminders are sent and participants who miss treatment for seven consecutive days will be excluded from the trial.

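### The arm comparison names no centre term although patients are recruited and randomised in three hospitals; adding centre is a free gain in efficiency, not a correction of bias

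*Protocol article*

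**What the plan says.** All statements are from the protocol article.

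- **Study design, paragraph on the treatment centres (after the Fig. 3 legend).** The main centre, an endocrinology and metabolism department, enrols all 60 healthy controls and 108 patients, who are randomised between the two experimental groups. The other two hospitals, one of them a maternal and child health hospital, "will enroll the other 108 participants, who will also be randomly assigned between the two experimental groups". Their 108 is a joint quota.
- **Study design.** The 216 patients are "randomly assigned to the two experimental (diagnosis) groups in a 1:1 ratio".
- **Randomization.** An SPSS random number generator and sequentially opened opaque envelopes are used. Strata, blocks and separate lists per centre are not mentioned.
- **Outcome measurements.** The primary outcome is change in PCOS condition, with the LH/FSH ratio as the main index.
- **Statistical analyses.** For quantitative indices, "Variance analysis will be used to compare the quantitative indices among the different groups (healthy control group and experimental groups 1 and 2"). For categorical ones, "The chi-squared test or exact probability method will be used to compare the qualitative indices among the three groups". Group is the only factor named.
- **Study limitations.** Consistent diagnosis in experimental group 1 is called the main difficulty, "because the diagnosis will be made by several different physicians".

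**The concern.** Outcomes in a multicentre trial often differ by centre, and there are reasons to expect it here. An endocrinology department and a maternal and child hospital may attract different mixes of hormone-type and lipid-type patients. Subtype determines the drug, so case mix could carry through to the LH/FSH ratio. In group 1 the subtype is assigned by several physicians; in group 2 it comes from metabolomic indices. Centre may therefore act differently in the two arms.

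If centre matters and is left out of the model, its variation stays in the error term. What is at stake is precision: intervals wider than they need be, and some power given up that the data already collected could supply.

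**Working it through.** **The plan's own figure.** The Sample size calculation gives 216 patients "with a significance level of 0.05 and a power of 0.80" and a 20% dropout allowance. It states no effect size, SD or test for the primary outcome, so 216 cannot be derived from the article. Trying pairs of the quoted sensitivities and specificities gives only accidental matches. For example, 86% against 96.7%, two-sided, gives 108 per arm, but with no allowance for dropout. The check below therefore takes 216 as given and works back from it.

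**Inputs**
- Two-sided alpha 0.05 ("All statistical tests will be double-sided") and power 0.80.
- Evaluable patients per arm: 108 × 0.8 = 86.4, taken as 86.
- rho, the share of outcome variance explained by centre: not stated, so 0 to 0.20 is assumed.

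**Step 1, implied standardised difference.** d = (1.960 + 0.842) × sqrt(2/86) = 0.427 for 80% power with the total SD as planning basis. Hence d/SE = 2.802.

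**Step 2, formulas**
- Ratio of unadjusted to adjusted SE: 1/sqrt(1 − rho).
- True size of the unadjusted test if allocation is balanced within centre: 2 × [1 − Phi(1.960/sqrt(1 − rho))].
- Power with centre in the model: Phi(2.802/sqrt(1 − rho) − 1.960).
- Power without centre, allocation balanced within centre: Phi((2.802 − 1.960)/sqrt(1 − rho)).
- Power without centre, allocation not stratified: about 0.80, with size about 0.05.

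**Step 3, example at rho = 0.10.** sqrt(0.90) = 0.9487. The SE ratio is 1.054. The size is 2 × [1 − Phi(2.066)] = 0.039. Power with centre is Phi(0.993) = 0.840. Power without centre, balanced, is Phi(0.887) = 0.813.

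**Step 4, results.** Gains are in power points.

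| rho | SE ratio | Size without centre, balanced | Power with centre | Power without, balanced | Gain, balanced | Power without, not stratified | Gain, not stratified |
|---|---|---|---|---|---|---|---|
| 0 | 1.000 | 0.050 | 0.800 | 0.800 | 0 | 0.80 | 0 |
| 0.05 | 1.026 | 0.044 | 0.820 | 0.806 | 1.4 | 0.80 | 2.0 |
| 0.10 | 1.054 | 0.039 | 0.840 | 0.813 | 2.7 | 0.80 | 4.0 |
| 0.15 | 1.085 | 0.034 | 0.860 | 0.819 | 4.1 | 0.80 | 6.0 |
| 0.20 | 1.118 | 0.028 | 0.879 | 0.827 | 5.2 | 0.80 | 7.9 |

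**Step 5, simulation check.** 172 patients were split 86/43/43 over three centres, with 4,000 runs per cell.
- rho 0.10, balanced: size 0.039 without centre and 0.050 with it; power 0.809 and 0.836.
- rho 0.10, not stratified: size 0.048 and 0.049; power 0.804 and 0.842.
- rho 0.20, balanced: size 0.033 and 0.054; power 0.822 and 0.873.
- rho 0.20, not stratified: size 0.053 in both; power 0.790 and 0.861.

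These agree with the formulas within simulation error.

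**Step 6, sensitivity to the anchor.** If the 80% is attached to the centre-adjusted analysis instead, unadjusted power under balanced allocation is Phi(2.802 − 1.960/sqrt(1 − rho)). This gives 0.785, 0.769, 0.750 and 0.729 at rho 0.05, 0.10, 0.15 and 0.20, so the loss at the top of the range is about 7 points instead of 5.

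**Step 7, cost of the centre term.** With 172 evaluable patients, residual degrees of freedom fall from 170 to 168, which is negligible even if rho is 0.

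**The case against.** **Silence is not a decision.** The section names variance analysis and chi-squared tests. It does not say that the variance analysis is one-way or that centre will be excluded. Covariates are commonly left to a full protocol or SAP, and neither is shown. This stands in part: one cannot conclude that centre will be omitted. But the article does list the levels of its group factor and its pairwise methods, so a concrete addition to that stated analysis is a fair request.

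**Quotas are not strata.** A reader might infer from the centre quotas that randomisation was stratified by centre. The Randomization section does not say so, and the wording fits a single unstratified list. This stands. The size figures below 5% apply only if allocation was balanced within centre. If the two quotas of 108 were the strata, variation between the two smaller hospitals would not be balanced, and the result would lie between the two cases in the table.

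**No between-centre variance is given.** A reader might call centre a known source of variation. The article reports no centre difference in any index, and the argument rests on hospital type and the number of physicians. Training, a test of consistent performance and a three-physician team for undecided cases work against such differences. Analysing change may also remove stable differences in level between centres. All of this stands, and is why the range starts at zero.

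**The unadjusted test is not wrong.** A reader might infer that standard errors ignore centre and are too small, giving false positives. The reverse holds: centre variation is counted in the residual, so the test has about its nominal size or is conservative.

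**Conclusion.** The point holds as a modest recommendation on efficiency. The stated analysis names no centre term, and including one would gain about 0 to 5 power points if allocation was balanced within centre, or about 0 to 8 if it was not stratified, for rho between 0 and 0.20. In the balanced case the nominal 5% test has a true size between 5% and 2.8%; otherwise its size stays near 5%.

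These figures rest on the assumed rho, 86 evaluable patients per arm, and 80% power at the total SD. The article does not support a claim of bias, inflated type I error or power below the 80% target: on this planning basis unadjusted power is 0.80 to 0.83, and no effect size or SD is stated from which an actual shortfall could be computed. The recommendation does not depend on how allocation was done, because adjustment helps in both cases whenever centres differ and costs almost nothing when they do not.

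**What to change.** 1. State whether allocation was balanced within centre.
2. Compare the two randomised arms in a linear model with arm and centre (three levels). Leave the healthy controls out of this model: all 60 come from the main centre, so at the other two hospitals there are no controls to compare with.
3. For binary outcomes, use a Mantel-Haenszel test stratified by centre.
4. Show the arm estimate by centre descriptively, because group 1 subtyping is done by several physicians.

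The cost is one extra factor in the model and two degrees of freedom. The centre of each patient is already held, the methods are available in the stated software, and no new data are needed. The change should be written down before the data are unblinded.
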